### 2.5. Sample size calculation

The effect indicators of our study are the electric characteristic and VAS score of *De Qi* sensation before and after warm needling. Based on the results of the previous experiment, which applied the semiconductor analyzer to 30 healthy individuals, the different electric characteristic of meridians was obtained by different input direction on the meridians.^[19]^ The electric currents in different directions were 0.49 ± 0.11 and 0.38 ± 0.13 in the Lung meridian.^[19]^ Another study showed that the VAS score of *De Qi* sensations in healthy participants were 1.54 ± 1.62 and 1.87 ± 1.88 in the traditional needle group and special needle group, respectively.^[18]^ Thus, we used G*Power 3.0.1.0 software to calculate our sample size, with power = 0.8, alpha = 0.05, effect size convention *R* = 0.53. The required sample size of each group was calculated to be 30 participants.

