## 2. Material and methods

### 2.1. Study design

This is a prospective and observational study that will be conducted by the Department of Chinese Medicine at the Kaohsiung Chang Gung Memorial Hospital and the Department of Physics at National Sun Yat-sen University from March 2022 to December 2022. The participants will be recruited from the students and staff at National Sun Yat-sen University. Our study will enroll 30 healthy participants in 1 group and all of them will receive both interventions, acupuncture and warm needling, and electric measurement. All personal data will be preserved in a locked closet and kept confidential until the end of the experiment when the principal investigator will disclose and analyze the results.

The participants will receive acupuncture, following which we will use a semiconductor analyzer to measure the electric characteristics and evaluate the visual analog scale (VAS) score before warm needling. Subsequently, we will place burned moxa on the acupuncture needles as our warm needling method. After the moxa burns out, we will measure the electric characteristics using the same evaluation method. We will analyze 1 meridian at a time and measure 12 meridians sequentially in this study. Therefore, all participants will undergo 12 sessions of measurements. Finally, we will compare individual electric characteristics data, before and after warm needling, on 12 meridians. The measurements will be completed in 1 day and the participants would not have to return for follow-up. The flow chart of the study design is presented in Figure 1.

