### 2.6. Statistical analysis

Paired *t* test and repeated measure two-way ANOVA will be used to analyze the change of electric characteristics and VAS between baseline data and post-warm needling data of each participant. We set the statistical significance at a *P* value of < .05. Our statistical analyses will be conducted using SPSS for Windows, version 22 (Statistics 22, SPSS, IBM Corp., Chicago, IL).

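### The planning effect size of 0.53 follows from neither set of figures cited for it, and the stated 80% power does not carry over to VAS

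*Protocol article*

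**What the plan says.** Section 2.5 names two effect indicators, the electric characteristic and the VAS score of De Qi sensation, each before and after warm needling. It cites one earlier result for each:

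- Current: "The electric currents in different directions were 0.49 ± 0.11 and 0.38 ± 0.13 in the Lung meridian".
- VAS: "1.54 ± 1.62 and 1.87 ± 1.88 in the traditional needle group and special needle group".

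A linking 'thus' leads from these to a G*Power run "with power = 0.8, alpha = 0.05, effect size convention", with the effect size written as "effect size convention *R* = 0.53". The result is: "The required sample size of each group was calculated to be 30 participants".

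Section 2.1 describes a single-arm design: "Our study will enroll 30 healthy participants in 1 group and all of them will receive both interventions". Section 2.4 makes the electric characteristics primary and VAS secondary. Section 2.6 names a paired t test and a repeated-measures two-way ANOVA for both, with this threshold: "We set the statistical significance at a *P* value of < .05".

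Section 2.5 does not say which test was entered in G*Power, which indicator 0.53 belongs to, or what within-participant correlation or SD of differences was assumed.

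**The concern.** An article may condense its sample-size reasoning. This one, however, prints both the inputs and the result, and the result does not follow from the inputs. One effect size is offered after two data sets whose standardised differences are almost five times apart (0.91 against 0.19).

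Two further features make the calculation hard to check. The effect size carries the label *R*, which suggests a correlation, and the result is given per group although there is only one group. The cited contrasts are also indirect: one compares input directions and the other needle types, and neither compares before with after warm needling.

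What is at stake is how the results can be read. VAS is part of the stated sample-size basis and will be tested at 0.05. A reader who takes 80% power to cover VAS would give a non-significant VAS result more weight than the cited figures allow. For the primary outcome, the planning effect has no traceable source.

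**Working it through.** **Inputs.** Power 0.80, alpha 0.05, effect size 0.53, N = 30, and the two sets of means and SDs, all from section 2.5; one group from section 2.1; paired t test from section 2.6. Two-sided testing is assumed because it reproduces N. The before/after correlation r is not given, so it is varied.

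**Step 1: reproduce N = 30.** For a paired t test with n pairs, the noncentrality is dz × √n on n − 1 degrees of freedom, where dz is the mean change divided by the SD of the within-participant differences. With dz = 0.53, two-sided 0.05:

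- n = 30: power 80.1%
- n = 29: power 78.7%

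So N = 30 is reproduced. Other readings of 0.53 do not give 30: a one-sided paired test gives 24, a two-sided comparison of two groups gives 57 per group, and a two-sided test of a correlation of 0.53 gives about 26.

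**Step 2: standardised differences from the cited figures.** d = |m1 − m2| / √((s1² + s2²)/2).

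- Current: 0.11 / √((0.0121 + 0.0169)/2) = 0.11 / 0.1204 = 0.91
- VAS: 0.33 / √((2.6244 + 3.5344)/2) = 0.33 / 1.7548 = 0.19

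The mean of the two is 0.55, which is also not 0.53 (dz = 0.55 would give N = 28).

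**Step 3: paired effect sizes and power at n = 30.** dz = |m1 − m2| / √(s1² + s2² − 2·r·s1·s2), two-sided 0.05, one paired test.

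| r (assumed) | Current dz | Current power | Current pairs for 80% | VAS dz | VAS power | VAS pairs for 80% |
|---|---|---|---|---|---|---|
| 0 | 0.646 | 92.8% | 21 | 0.133 | 10.9% | 446 |
| 0.5 | 0.907 | 99.8% | 12 | 0.187 | 16.8% | 227 |
| 0.8 | 1.406 | >99.9% | 7 | 0.291 | 33.8% | 95 |
| 0.9 | 1.927 | >99.9% | 5 | 0.401 | 56.5% | 51 |
| 0.95 | 2.571 | >99.9% | 4 | 0.541 | 81.7% | 29 |

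**Step 4: the correlation that would give dz = 0.53.** Set the SD of differences to |m1 − m2| / 0.53 and solve for r.

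- Current: 0.11 / 0.53 = 0.2075, squared 0.0431; r = (0.0290 − 0.0431) / 0.0286 = −0.49
- VAS: 0.33 / 0.53 = 0.6226, squared 0.3877; r = (6.1588 − 0.3877) / 6.0912 = +0.95

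The two indicators would need very different correlations, and the one for current is implausible for repeat readings on the same person.

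**The case against.** The case on the other side has real force.

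- **The primary outcome is not short of power.** On the cited currents, 30 participants are more than enough for a single test, and planning at 0.53 is more cautious than 0.65 to 0.91. This stands. It answers any charge of under-powering for that comparison, but not the missing derivation.
- **The arithmetic from 0.53 to 30 is right.** This stands. The two-group and correlation readings are excluded by sections 2.1 and 2.6; they show only that the labels are wrong.
- **VAS power depends on an unstated correlation.** This stands. The readings come from one person in one session, with a burn time of about 5 to 10 minutes between them, so r above 0.5 is plausible. A reader might infer that the 80% is simply false for VAS, with true power of 11 to 17%. The document does not support that: the band holds only for r between 0 and 0.5.
- **The ANOVA may use more data.** If VAS is rated at each of the 12 meridians, which the article does not say outright, averaging 12 changes helps. With correlation ρ between meridian changes, dz is divided by √((1 + 11ρ)/12). Power is then 66%, 48% and 27% at r = 0.5 with ρ = 0.1, 0.2 and 0.5, and 85% and 55% at r = 0.8 with ρ = 0.2 and 0.5. So it cannot be said that VAS has almost no chance of success. Nor does this rescue the stated figure: N = 30 reproduces as a single paired test, and section 2.5 mentions no such averaging.
- **The cited VAS contrast is indirect.** If needle type is not the effect under test, it cannot fix the true VAS power. This stands as a limit: the figures above test the plan against its own inputs and do not predict the result.
- **The article never assigns 0.53 to an indicator.** True. That 80% is claimed for both is a reading of the paragraph, invited by naming both indicators and linking both data sets to the one calculation.

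**Conclusion.** The point holds as a fault in the basis of the sample size, not in the sample size itself. The 0.53 is presented as following from the cited studies and follows from neither. The 80% power is correct for a two-sided one-group paired t test at dz = 0.53 and for nothing else that the section describes.

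For a single test of current at the cited difference, there is no shortfall for any r above about −0.49. For VAS at the cited difference, a single paired test falls below 80% unless r is about 0.95. These results rest on two-sided testing, on the cited means and SDs taken at face value, and on an assumed r. They do not show what power the trial will have for the warm-needling effect, because the cited contrasts are different ones.

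Severity: should be fixed. N, design and analysis are unchanged, and the demonstrable consequence falls on a secondary outcome.

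**What to change.** Keep N = 30 and restate section 2.5:

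1. Describe a one-group paired calculation: 30 pairs give 80% power at two-sided 0.05 to detect a mean change of 0.53 SD of the within-participant differences, for a single electric comparison.
2. Remove the label *R*, the per-group wording and the implication that 0.53 was derived from the cited studies. If those studies stay as background, say that their contrasts are only indirect for the warm-needling comparison.
3. State that the 80% does not extend to VAS. Give its power as a range with the assumed correlation beside each figure (paired t test at the cited difference: 11% at r = 0 to 57% at r = 0.9), and report VAS as an estimate with a 95% confidence interval.

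The cost is the rewording of one section and a less favourable stated power for VAS. No participants or measurements are added.

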### 2.6. Statistical analysis

Paired *t* test and repeated measure two-way ANOVA will be used to analyze the change of electric characteristics and VAS between baseline data and post-warm needling data of each participant. We set the statistical significance at a *P* value of < .05. Our statistical analyses will be conducted using SPSS for Windows, version 22 (Statistics 22, SPSS, IBM Corp., Chicago, IL).

### 2.7. Data monitoring

Acupuncture, EA, and warm needling are general practices in TCM. Minor adverse side effects of acupuncture and EA include minor bruising, bleeding or pain at needle insertion sites,^[24]^ nausea, sweating, and dizziness.^[25]^ Other complications include pneumothorax and septicemia. Most adverse side effects are minor, and serious complications are rare.^[25]^ The most common adverse events related to warm needling are burns, skin rash, and pain.^[7]^ Warm needling therapy has been reported as a safe method in clinical practices.^[4]^ In our study, acupuncture will be performed by qualified doctors and the acupoints we chose are at the 4 limbs. The procedure will be safe with minimal risk of serious adverse events. The device we use for EA will apply voltage from 1 to 60 V and current under 2 mA. The voltage and current are in the therapeutic range, which means that our study is safe. Additionally, we will perform warm needling, which adds moxa on acupuncture needles and introduces heat stimulation through the needles, and thick cardboard will be placed on the skin surface to prevent burning injury. If serious adverse effects of acupuncture occur, such as fainting or general weakness, the doctor will remove the acupuncture needles and stop the intervention immediately, and we will record the reason for dropping out of the study.

## 3. Discussion

 Some reviews of animal models discussed the mechanism of warm needling; however, most of these investigated molecular biological mechanisms. Warm needling regulated cytokines such as interleukin-1β,^[26]^ tumor necrosis factor-α,^[27]^ and transforming growth factor-β1^[28]^ to inhibit the inflammatory response. Warm needling also inhibited the overexpression of insulin-like growth factor-1 to achieve the effects of improving pathological changes in the tissue.^[28]^ Besides, warm needling modulated nicotinamide adenine dinucleotide phosphate oxidase 2 and superoxide dismutase 2, which are associated with oxidative stress.^[26]^ Chondrocyte cytoskeletal proteins such as Rho-associated protein kinase, phospho-cofilin, and monopherine domain kinase 1 were down-regulated by warm needling, which relieved symptoms of osteoarthritis.^[29]^ Histopathological changes observed using transmission electron microscopy showed an increase in the number of organelles with rearrangement and redistribution of the extracellular matrix after intervention with warm needling.^[30]^ Moreover, warm needling down-regulated matrix metalloproteinase-3, thereby influencing tissue remodeling.^[27]^ However, few studies are present on physical characteristics related to meridians and warm needling. In the present study, we will introduce physical parameters to measure the meridians and explore warm needling through physical perspectives.

According to the World Health Organization International Standard Terminologies On Traditional Medicine In The Western Pacific Region, warm needling is a practice of acupuncture in which the needle is warmed during needling by placing a burned moxa stick on the handle of the needle after insertion.^[31]^ This therapeutic technique delivers heat at acupoints to stimulate the circulation of Qi and blood. In TCM theory, this procedure achieves the effect of a warm supplement, which means to activate and restore a decreased function to normal.^[31]^ In the present study, EA, through the semiconductor analyzer Agilent B1500A/Agilent 4156C, applied the same voltage before and after warm needling. Recent meridian studies showed that the meridian has electric characteristics and physical properties.^[17]^ Additionally, improving the conductivity of the meridians could cause higher electric current and lower impedance in the meridians, which could enhance de-qi sensations and increase the therapeutic effect.^[32]^ Since there are different acupuncture manipulations in traditional Chinese theory, a previous study revealed that the electric current measured during acupuncture was significantly larger in supplementation manipulation than in draining manipulation in the meridians.^[20]^ Accordingly, we expected the changing electric characteristics to a higher current after warm needling would be comparable with the current measured before warm needling since warm needling is a supplementation method. There will be new physical discoveries of warm needling, acupuncture plus moxibustion, in our study.

Although the therapeutic effects of warm needling have been affirmed clinically, the mechanism of warm needling has not been widely elucidated. Few studies discussed the association between ionic conductivity and change of temperature in the biophysical field. This is an interdisciplinary study that has not been performed before, whereby TCM professionals cooperated with physics professionals, toward exploring warm needling using new methods and interventions. The results of electric characteristics related to warm needling will give a new perspective on this popular and effective TCM treatment. The electrical intervention and electric characteristics of warm needling are expected to have vast applications in medical treatment.

## 4. Ethics and dissemination

This protocol was approved by the Human Ethics Committee of Chang Gung Medical Foundation Institutional Review Board, IRB No. 202101924A3. The protocol has been registered at ClinicalTrials.gov (Identifier: NCT05249010) and ISRCTN.com (Identifier: ISRCTN82061181). All participants will provide written informed consent before enrollment. Personal information about potential and enrolled participants will be collected, shared, and maintained in an independent closet to protect confidentiality before, during, and after the trial. Data will be available under reasonable request.
